### Study Procedures

All full-time therapists at both study sites who volunteer to participate will be consented. We project 4 therapists at each site (N=8) will participate. As in the authors’ previous work [79], clinic staff will discuss the research opportunity with the families of all the adolescents during routine intake procedures. If consent is given, clinic staff will send the family’s contact information to the study team through secure channels. The study team will contact interested caregivers by phone to complete (1) consent to phone screen, audio record sessions, complete outcome interviews and questionnaires, and grant access to clinic records and (2) an eligibility screener assessing IDs. IDs will be assessed using the Achenbach System of Empirically Based Assessment Child Behavior Checklist [122], a well-validated assessment method for screening for depression and anxiety problems in youth. IDs will also be assessed during the baseline research assessment using the Mini-International Neuropsychiatric Interview for Children and Adolescents [123,124], a structured diagnostic interview administered by lay interviewers; the interview yields Diagnostic and Statistical Manual of Mental Disorders, Fifth Edition, Text Revision categories and has been used in diverse adolescent samples [79,125]. Client data on protocol viability (limited to Fam-AID cases only) and clinical outcomes will then be collected on all study clients (regardless of amount of treatment participation) at baseline, 3-month, and 6-month follow-up using REDCap (Research Electronic Data Capture; Vanderbilt University) cloud software, a widely used and secure Health Insurance Portability and Accountability Act (HIPAA)–compliant, web-based data collection platform.

Clinicians in both conditions will be asked to complete a self-report fidelity measure after every session with a study client. They will also be asked to audio record all sessions, a minimally intrusive procedure that is widely accepted by families and therapists in previous work [94]. Data will be collected using web-based links and uploaded to secure servers. As per the study team’s numerous observational fidelity studies [126-130], 1 session will be randomly selected from the early phase of treatment (sessions 1 to 3) and 2 from the later phase (sessions from session 5) of each client for coding with an observational version of the Fam-AID Fidelity Checklist (described in the Study Measures section). Fidelity observational coders will be trained by the study team using gold standard procedures [126,131-133] and kept naive to the study condition.

### Study Measures

#### Fam-AID Fidelity Checklist

This study will use an adapted version of the Inventory of Therapy Techniques (ITT [95,96]), a postsession therapist-report fidelity tool that requires 1 or 2 minutes to complete. ITT items are designed to measure the extensiveness (ie, thoroughness and frequency) with which a given treatment technique was used on a 3-point Likert-type scale: 0 (not at all), 1 (a little bit or moderately), or 2 (quite a bit or extensively). ITT items are derived from treatment protocols and their associated observational fidelity tools, for example, for family therapy [51] and for CBT [67], after being vetted for relevance by community clinicians in multiple treatment settings [134]. ITT has shown strong construct [50,134] and predictive [79,135] validity in studies with adolescents receiving family therapy and CBT in usual care. The Fam-AID Fidelity Checklist mimics the ITT structure, containing multiple items in each of the 5 Fam-AID modules: culturally attuned family engagement, relational reframing of ID symptoms, functional analysis of ID symptoms, CBT treatment techniques for ID, and SUD+ID education and safety planning. The Fam-AID Fidelity Checklist–Observer Version is an identical measure with instructions for observer coding.

#### Protocol Acceptability

Protocol acceptability interviews will be held with therapists and clients who participate in the Fam-AID protocol. Therapists will be interviewed in agency-based focus groups. Clients will be interviewed at the 6-month follow-up assessment point; adolescents and caregivers will be interviewed separately. Interview content will be adapted from existing treatment feasibility and acceptability interviews (refer to the study by Cho et al [136]) and include the following questions:

What are the overall impressions of Fam-AID for use in routine practice (therapist; open-ended)?How effective and/or difficult it was to use Fam-AID for individual cases compared to usual practice? (therapist, Likert-type rating)Was it important for you (your caregiver) to be included in treatment? (client, open-ended)How much did emotion coping training help you (your child)? (client, Likert-type rating)

#### Adolescent and Family Outcomes

Clinical record data will be collected on the number of treatment sessions attended by family members, along with the data on adolescent attendance. Difficulties in Emotion Regulation Scale [137,138] is a 16-item measure of 6 aspects of emotion regulation: nonacceptance, engagement in goal-directed activities, impulsivity, emotional awareness, access to emotion regulation strategies, and emotional clarity. It uses a 5-point Likert scale and has shown acceptable test-retest reliability and internal consistency in adolescent populations [137-140]. The Revised Children’s Anxiety and Depression Scale-Child and Parent version [141] is a 47-item measure of an adolescent’s anxiety and depressive symptoms. The Revised Children’s Anxiety and Depression Scale-Child version contains 6 *Diagnostic and Statistical Manual of Mental Disorders, Fifth Edition, Text Revision*–linked subscales: separation anxiety, social anxiety, generalized anxiety, obsessive-compulsive disorder, panic disorder, and major depressive disorder. A total anxiety subscale score sums 37 items from the 5 anxiety subscales; the major depressive disorder subscale score sums 10 items. The Revised Children’s Anxiety and Depression Scale-Parent version is identical to the Revised Children’s Anxiety and Depression Scale-Child version, but the wording of the items is from the parents’ perspective. The Revised Children’s Anxiety and Depression Scale-Child and Parent version have exhibited strong and acceptable internal consistency, respectively [142-144]. CRAFFT [145,146] is a widely used and well-validated adolescent-report tool that measures patient use of alcohol, cannabis, nicotine, illegal drugs, prescription medication, or anything else to get high in the past year and the past 3 months. It also asks about riding in a car driven by someone (including self) who was intoxicated. If SU is reported, the tool asks 5 additional questions: use to relax, use while alone, forget things you did while intoxicated, family or friends tell you to reduce use, and gotten into trouble while using. Parent-Teen SUD+ID Communication Frequency [147] is a 6-item adolescent and caregiver report of how often parents and teens talk to one another about key SUD-ID issues (eg, health risks of SU and ID and discipline regarding SU); response are scored on a 5-point scale, ranging from *never* to *very often* (refer to the studies by Sherman and Ehrenreich [77], Hogue et al [78], and Hogue et al [79]). Parent-Teen SUD+ID Communication Quality [148] is a 6-item adolescent and caregiver report on the quality of communication between parent and adolescent about SUD+ID issues (eg, my caregiver/child and I are interested in each other’s opinions about SUD+ID, and if my caregiver/child and I talk about SUD+ID, I feel understood); responses are scored on a 5-point scale, ranging from *not at all* to *very much* (refer to the studies by Koning et al [147] and Carver et al [149]).

### Plan of Analyses

*Aim 1 acceptability* analyses (Fam-AID condition only) will explore protocol acceptability and perceived effectiveness through formative qualitative interviews with staff and clients. Interviews will be recorded, transcribed, and then analyzed inductively [150] for data relevant to feasibility and acceptability. Two research staff members will separately code interviews for emerging concepts using thematic content analysis [151], an approach that applies inductive coding to identify themes within the data. Initial analysis will identify concepts through open coding [152]; inter-rater reliability checks will then be used to compare themes generated and resolve conflicts, and coding will continue to the point of saturation, that is, when no new concepts emerge.

*Aim 1 fidelity benchmarks* analyses (Fam-AID condition only) will examine both types of previously described fidelity metrics. Regarding coverage, descriptive statistics will capture frequencies related to (1) proportion of clients who received at least 1 intervention from each of the 5 modules and (2) interventions from which modules were most or least favored across clients. Chi-square analysis will be used to compare study conditions on the proportion of clients who received adequate coverage and conduct one-way analysis of variance to assess mean differences across modules in the Fam-AID condition to evaluate module preferences among therapists. Regarding dose, statistical equivalence testing [153] will be used to examine whether clinicians’ average scores for intervention extensiveness on both observer- and therapist-report versions of the Fam-AID Fidelity Checklist are equivalent to a designated benchmark, which will be set (granting appropriate latitude for a pilot trial) for each module as mean 2.5 (SD 0.50). A CI approach will be adopted in which an equivalence interval is defined as the benchmark +10% and –10%. Next, a CI is defined by the following formula: CI_90%_=M_R_–M_T_+/–z_α_(S_MR−MT_). In this equation MR represents the benchmark module mean, MT the average module score for study therapists, zα the critical one-tailed value from the z distribution for the chosen value of α, and SMR−MT the pooled SE. If the calculated CI falls within the equivalence interval, equivalence can be concluded. In addition, therapist variability in Fam-AID fidelity will be examined via statistical process control analyses (refer to the study by Hogue and Dauber [125]) in which individual therapist fidelity scores are plotted on a control chart to check for meaningful variation compared to control limits represented by the designated fidelity benchmark.

*Aim 2a family attendance* will involve between-condition comparison of treatment sessions attended by family members other than the adolescent. Linear mixed effects (LME) modeling will be used to examine the effect of condition on attendance counts. The model will include fixed effects for independent variables (ie, condition) and random effects to account for nesting at the therapist level, thereby providing unbiased parameter estimates [154,155]. Nesting at the client level will not need to be controlled in these analyses, as client summed totals will serve as a dependent measure: tallies of sessions attended by family members will be summed across the follow-up period. The LME models package [156] will be used; it provides full information maximum likelihood estimation and restricted maximum likelihood estimation, both of which produce unbiased parameter estimates based on the assumption that data are missing at random and outperform other missing data approaches even when missing at random is not met [157]. Effect sizes will be indexed by η_2_ [158]. However, the nonlinear mixed effects model will be used if the assumption of continuous data is not tenable (eg, when attendance counts are not normally distributed).

*Aim 2b adolescent and family outcomes* analyses will involve similar LME models previously described. To test for change over time, each model will include fixed effects for time (months since baseline, coded as 0, 3, and 6) and random effects for (1) nesting of clients within therapists and (2) repeated measures within person across follow-up. Hypotheses will be tested by adding condition as a fixed effect and examining the condition-by-time interaction on each outcome in separate models. Acknowledging that outcomes may not demonstrate sharp trajectory change during the relatively brief 6-month follow-up window, the intercept will be set at the terminal assessment point by recoding time points (–6, –3, and 0); in doing so, the condition effect for the intercept will reflect a between-group difference at 6-month follow-up. LME modeling is recommended as an alternative to traditional modeling techniques for longitudinal designs with small samples [159].

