### Study Condition: TAU Only

Previous research on TAU intervention delivery at both study sites using therapist self-report [95] and observational data from session recordings [96] indicates that site therapists routinely deliver relatively low-dose quantities of evidence-based SUD treatment techniques, favoring motivational interviewing and addiction counseling techniques, with even less delivery of CBT or family therapy techniques for SUD. Sites do not have existing protocols for treating IDs as either main referral problems or cooccurring conditions.

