### Fam-AID Training and Fidelity Monitoring

Site clinicians will be trained for 6 hours. The session will feature video-based training [117,118] in Fam-AID modules and techniques. Thereafter, consultation at each site will include bimonthly live consultation with a protocol expert focused on equipoise between protocol fidelity and case tailoring, along with continuous feedback from therapist- and observer-report fidelity data, which is emailed directly to clinicians and used in live consultation to enable rapid adjustment in protocol delivery [119-121]. Two main fidelity benchmarks will be monitored for each case. These benchmarks include clinicians delivering interventions for every module in at least 1 treatment session (ie, coverage) and clinicians performing at or above the mean scale score for intervention extensiveness on the Fam-AID Fidelity Checklist (described in the Study Measures section) for at least 1 technique from each module (ie, dose), with both therapist- and observer-report checklist versions being tracked.

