### Study Power

Aim 2 analyses will compare study conditions based on family attendance and client outcomes over time, with client (N=60) as the unit of analysis. Assuming α=.05, a total sample size of N=60 (with 30 clients per condition), 3 measurement occasions with a moderate intercorrelation (*r*=0.50), and a moderate effect size of Cohen *d*=0.60, the analysis yields a power of 0.80. A smaller effect size of Cohen *d*=0.50 yielded a power of 0.65, assuming α=.05. These estimates are in line with the impacts seen in the studies on adolescents with ID but not SUD [60,62] and in the studies on adolescents with SU problems treated in usual care [79,94].

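### The between-condition coverage test uses only whether all five modules were delivered; if full coverage under Fam-AID is low, it can miss a doubling of modules delivered

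*Protocol article*

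**What the plan says.** Fam-AID Training and Fidelity Monitoring defines the first of two per-case benchmarks as "clinicians delivering interventions for every module in at least 1 treatment session (ie, coverage"). Specific Aims of the Study puts the same question for Aim 1. Plan of Analyses uses the matching statistic, "proportion of clients who received at least 1 intervention from each of the 5 modules", and then specifies the test: "Chi-square analysis will be used to compare study conditions on the proportion of clients who received adequate coverage". It does not define adequate coverage separately, so all five modules or not is the natural reading.

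That paragraph is labelled as covering the Fam-AID condition only, although this sentence compares Fam-AID with TAU. Its other analyses are not between-condition tests: a description of "interventions from which modules were most or least favored across clients", an analysis of variance across modules within Fam-AID, an equivalence test of dose against a benchmark, and therapist control charts.

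The data for a finer comparison will exist. Study Procedures states: "Clinicians in both conditions will be asked to complete a self-report fidelity measure after every session with a study client". Three sessions per client are also coded by observers who are kept naive to condition. The sample is "a total sample size of N=60 (with 30 clients per condition").

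**The concern.** Each client has a number of modules covered, from 0 to 5. The planned test cuts that number at its top value, so a client who received four modules counts the same as one who received none. If few Fam-AID clients reach all five, the test rests on a handful of cases and ignores every partial increase. The study could then report no difference in coverage although training had doubled the modules delivered.

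Low full coverage is possible under this design:

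- The Discussion lets clinicians select modules by client need.
- When family members cannot be engaged, the TAU+Fam-AID overview names only modules 3, 4 and 5 as deliverable.
- Observer-rated full coverage requires all five modules to appear within three sampled sessions.

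**Working it through.** **Inputs.** From the article: 30 clients per condition, α=0.05 (taken as two-sided), five modules. Assumed, because the article gives no coverage rates: all delivery rates and the correlation between modules within a client.

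**The plan's own figures.** No power is stated for the coverage test. The Aim 2 figures do reproduce. Averaging three occasions at r=0.50 multiplies the variance by (1+2×0.5)/3=0.667, and a noncentral t with 58 df gives 0.799 at d=0.60 and 0.645 at d=0.50, against the stated 0.80 and 0.65. They do not bear on this test.

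**Step 1: smallest significant result if TAU is 0/30.** For 4/30 versus 0/30, chi-square = 60×(4×30−0×26)²/(30×30×4×56) = 4.29, p=0.038. For 3/30 it is 3.16, p=0.076. Fisher's exact p for 4/30 is 2×C(30,4)/C(60,4) = 2×27,405/487,635 = 0.11. For 5/30 it is 0.052 and for 6/30 it is 0.024. So uncorrected chi-square needs four fully covered Fam-AID clients and Fisher needs six. The expected count per condition is half the total number of all-five cases, so it is below 5 whenever that total is under 10.

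**Step 2: power by true all-five rate in Fam-AID.** With TAU at 0%, chi-square power is P(X≥4) and Fisher power is P(X≥6), for X~Bin(30, p). The last column is by exact enumeration.

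| Fam-AID all-five | Chi-square, TAU 0% | Fisher, TAU 0% | Chi-square, TAU 5% |
|---|---|---|---|
| 10% | 0.35 | 0.07 | 0.11 |
| 15% | 0.68 | 0.29 | 0.26 |
| 20% | 0.88 | 0.57 | 0.45 |
| 25% | 0.96 | 0.80 | 0.63 |
| 30% | 0.99 | 0.92 | 0.78 |
| 35% | 1.00 | 0.98 | 0.88 |
| 40% | 1.00 | 0.99 | 0.94 |

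At a given Fam-AID rate, power is higher when TAU is at 0 than when it is at 5% (at 20%: 0.88 versus 0.45). A TAU floor is therefore not the cause of the loss.

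**Step 3: the same data kept as a count.** Modules per client are binomial(5, p), or beta-binomial with within-client correlation 0.2. Chi-square power is by exact enumeration; rank-test (Mann-Whitney) power is by simulation. With independent modules the all-five rate is p⁵, for example 0.6⁵=7.8%.

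| Per-module rate, TAU v Fam-AID | Correlation | Mean modules | All-five rate | Chi-square | Rank test |
|---|---|---|---|---|---|
| 30% v 60% | 0 | 1.5 v 3.0 | 0.2% v 7.8% | 0.19 | >0.99 |
| 30% v 60% | 0.2 | 1.5 v 3.0 | 2.7% v 18% | 0.57 | 0.97 |
| 30% v 70% | 0 | 1.5 v 3.5 | 0.2% v 17% | 0.74 | >0.99 |
| 30% v 70% | 0.2 | 1.5 v 3.5 | 2.7% v 30% | 0.90 | >0.99 |
| 30% v 80% | 0 | 1.5 v 4.0 | 0.2% v 33% | 0.99 | >0.99 |

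A latent-correlation model (0.4) for 30% v 60% gives 0.60 against 0.96.

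**Step 4: observer version.** Let a module appear in a session with probability q, independently over three coded sessions, so coverage per module is 1−(1−q)³. With q=0.10 in TAU this is 0.271, a mean of 5×0.271=1.4 modules. With q=0.30 in Fam-AID it is 0.657, a mean of 3.3 and an all-five rate of 0.657⁵=12%. Chi-square power is 0.49, against about 1.00 for the rank test.

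**The case against.** The best defence is that all five modules is the study's own feasibility criterion, stated in the aims and again as a benchmark, so testing conditions on it answers the question the study asks. If over 90% of Fam-AID clients miss the benchmark, a non-significant coverage result does not mislead about the benchmark. That stands, and it is why the all-five proportion should stay.

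Several features also favour high coverage: one session per module suffices, several modules can be completed in one session, sequential delivery is the default, and clinicians receive training, consultation and fidelity feedback. Independence between modules is the harshest assumption, and correlation narrows the gap. The rank-test figures ignore therapist clustering, as does the planned chi-square, and the proposed mixed model was not simulated. These points limit the size of the finding but do not remove it.

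A reader might infer that TAU sitting at the floor makes the test fail. Step 2 shows the opposite. Nor is the floor a fact. The TAU Only section says "Sites do not have existing protocols for treating IDs as either main referral problems or cooccurring conditions", which makes a near-zero rate plausible, but Study Design Limitations and Strengths allows for some ID-targeted practice in TAU. A reader might also infer that the test will miss a real change, or that it conveys no effect size. The article supports neither: nothing in it shows that low full coverage is expected, and a difference in proportions is an effect size on the benchmark scale.

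**Conclusion.** The point holds in a limited form. Read as all five or not, the only stated between-condition test of clinician delivery discards a count that costs nothing extra to use. If full coverage under Fam-AID is below roughly 20-25% with TAU near 0, its power to register a doubling of mean modules is about 0.2 to 0.6, against 0.96 or more for the count. In the same range the uncorrected chi-square is unreliable, because significance at 4/30 versus 0/30 depends on which version of the test is used. The cause is the low all-five rate under Fam-AID. With TAU near 0 the loss is gone at about 35% full coverage; with TAU at 5% it takes about 50% (chi-square power 0.99). All rates are assumptions. This is a secondary Aim 1 check in a pilot, so the change is a cheap improvement and not a correction on which the study depends.

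**What to change.** In the coverage part of Plan of Analyses:

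- Define adequate coverage explicitly.
- Make the between-condition comparison on the number of modules covered per client (0-5), by an ordinal or binomial (x of 5) model with condition as fixed effect and a therapist random effect as in Aim 2. Run it for the therapist-report and observer-report checklists separately. Name a simpler fallback, since about 8 therapists may not support the random effect.
- Keep the all-five proportion as the stated benchmark, reported by condition with a confidence interval and, if tested, with an exact test in place of chi-square.
- Adjust the paragraph's Fam-AID-only label so that it admits this comparison.

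The cost is wording and one additional analysis on the same clients and data. The new result is on the module-count scale and not the benchmark scale, so the two should be reported together.

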Longitudinal outcome data suggest that adolescents with cooccurring SUD+ID are more difficult to treat effectively than those who do not have IDs. One systematic review [9] found that adolescents with comorbid SUD and depression showed higher attrition from treatment, and generally worse outcomes for both SU and depression, than those with a singular disorder. Another study [10] reported that baseline levels of elevated ID symptoms or diagnosis of an anxiety or depression disorder broadly predicted worse SU outcomes. Studies have also shown that maintenance of SUD treatment gains [11,12] and posttreatment recovery to adaptive levels of functioning [13] are harder to achieve for adolescents with IDs and related negative affect. It also appears that ID-related symptoms impact posttreatment SU behavior in multiple ways, foremost being that negative affect can induce adolescents to reinitiate use [14] or interfere with their motivation and capacity to use relapse prevention and health promotion skills learned during treatment [15].

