**Inclusion criteria**
The adolescent is aged 13 to 18 years.The adolescent lives with a primary caregiver who can attend treatment sessions.The adolescent endorses ≥1 *Diagnostic and Statistical Manual of Mental Disorders, Fifth Edition, Text Revision* [93] symptom for substance use disorder and meets the American Society of Addiction Medicine criteria for outpatient substance use treatment.The adolescent meets the *Diagnostic and Statistical Manual of Mental Disorders, Fifth Edition, Text Revision* criteria, or has elevated symptoms and impairment, for an ID, with the following expected to be most common: current or recurrent major depressive episode, pervasive depressive disorder, social anxiety disorder, generalized anxiety disorder, panic disorder, and posttraumatic stress disorder.The adolescent completes intake and is enrolled as an active case at the study site.

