### Study Condition: TAU+Fam-AID

#### Overview

Fam-AID will contain 5 modular components to be delivered in any order and to the extent indicated based on case status [37,43,97]. Modules can be individually or collectively completed in 1 session, staggered across sessions, and interspersed with other interventions. The time required to complete each module will vary based on client profile, practice habits of the provider, and case progress. Fam-AID will have standardized options for versatile delivery with individual adolescents alone whenever family members cannot be engaged in services; modules 3 and 4 can proceed intact, and module 5 can be adjusted for adolescent-only delivery. The study will be halted if it appears that Fam-AID delivery induces clinical harm. The following is a description of the projected module content, considering that the ultimate set of modules and their content will be determined over the course of the study:

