Fam-AID contains 5 modules, each consisting of core treatment techniques that have a strong evidence base. In keeping with the principles of modular intervention design [36,160,161], clinicians are invited to select and implement any Fam-AID module, in any order, based on client needs, with a default of delivering them sequentially. The 5 Fam-AID modules are intended to galvanize and reinforce the family support system and equip the adolescent to cope with and ameliorate ID problems. Notably, module 4 draws its menu of core CBT techniques to treat ID-related problems (emotional acceptance, emotional exposure, and behavioral activation) from an existing evidence-based transdiagnostic protocol, which treats the underlying negative affect and emotional dysregulation [77] associated with adolescent IDs. In these ways, Fam-AID is distinct from other adolescent SUD+ID options due to how it combines a core elements strategy, family-focused interventions, and individual CBT techniques, which might enhance the often modest long-term impact of interventions for ID symptoms in usual care [162].

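### The one-way ANOVA across the five Fam-AID modules cannot be read as therapist preference, because default order with early stopping, absent families and case need also move the module means

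*Protocol article*

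**What the plan says.** The Plan of Analyses (Aim 1 fidelity benchmarks, coverage) describes which modules were used most and least across clients, and will then "conduct one-way analysis of variance to assess mean differences across modules in the Fam-AID condition to evaluate module preferences among therapists". It mentions no conditioning on number of sessions, family presence or client need.

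Other sections set how modules are delivered:

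- Discussion, Overview: clinicians may choose any module "in any order, based on client needs, with a default of delivering them sequentially".
- Study Condition: TAU+Fam-AID, Overview: modules are "delivered in any order and to the extent indicated based on case status". They may be completed singly or several in one session. When family members cannot be engaged, "modules 3 and 4 can proceed intact, and module 5 can be adjusted for adolescent-only delivery". No adolescent-only option is named for modules 1 and 2.
- Inclusion criteria: "The adolescent lives with a primary caregiver who can attend treatment sessions".
- Study Procedures: client data are collected "regardless of amount of treatment participation".
- Introduction: a cited review found that adolescents with comorbid SUD and depression "showed higher attrition from treatment".

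**The concern.** A comparison of module means measures preference only if every module had the same chance of being delivered and was equally needed. The protocol's delivery rules do not ensure that, for three reasons.

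1. **Order with early stopping.** Under the sequential default, a case that ends early may never reach the later modules, yet it still counts as a Fam-AID case.
2. **Family absence.** Modules 1 and 2 may not be deliverable when no family member is engaged.
3. **Case need.** Modules are chosen and dosed by what the client needs, so a mean can reflect the case mix rather than the therapist's inclination.

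At stake is an interpretive conclusion of the pilot. A module described as unpopular might only have been out of reach, and training or module revision could be directed at the wrong problem. The reverse also matters: if two of these forces cancel, a flat result could hide a real preference.

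**Working it through.** **The plan's own figure.** The protocol gives no power or expected result for this ANOVA. Its only design calculation is the Aim 2 power, which does not bear on the point.

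**Inputs from the protocol.** 30 Fam-AID clients; 5 modules; α = 0.05 (stated for Aim 2, assumed here).

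**Assumptions not in the protocol.** Chance h of stopping after each session; share q of cases in default order (the rest in random order); share f of cases without family, in which modules 1 and 2 are skipped and 3 to 5 move forward. Binary coverage and one module per session. Therapists use every module they can reach, so there is no preference.

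**Step 1: expected coverage, all cases in default order.**

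- Stopping only, module j: (1 − h)^(j−1). At h = 0.10: 1.00, 0.90, 0.81, 0.73, 0.66.
- Absence only: 1 − f for modules 1 and 2, and 1 for the rest. At f = 0.20: 0.80, 0.80, 1.00, 1.00, 1.00.
- Both, modules 1 and 2: (1 − f)(1 − h)^(j−1). Modules 3 to 5: (1 − f)(1 − h)^(j−1) + f(1 − h)^(j−3).
- At h = 0.10 and f = 0.20: 0.80; 0.80 × 0.90 = 0.72; 0.80 × 0.81 + 0.20 × 1 = 0.85; 0.80 × 0.729 + 0.20 × 0.90 = 0.76; 0.80 × 0.656 + 0.20 × 0.81 = 0.69.

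The first pattern falls with module number, the second penalises modules 1 and 2, and the third is much flatter. None contains any preference.

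**Step 2: how often the one-way ANOVA rejects (simulated, no preference).**

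| Default-order share q | Stopping h | Absence f | Rejection |
|---|---|---|---|
| 100% | 5% | 0 | 0.37 |
| 100% | 10% | 0 | 0.90–0.92 |
| 100% | 15% | 0 | over 0.99 |
| 50% | 5% | 0 | 0.04 |
| 50% | 10% | 0 | 0.15–0.17 |
| 100% | 0 | 20% | 0.88–0.90 |
| 100% | 0 | 30% | 0.99 |
| 100% | 5% | 10% | 0.055 |
| 100% | 10% | 10% | 0.30 |
| 100% | 10% | 20% | 0.09–0.11 |
| 100% | 15% | 20% | 0.29 |

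Ranges are spread between simulation runs.

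**Step 3: a different delivery model.** Here each module needs 1 to 4 sessions, with the same distribution for all five, and the score is the number of sessions given to it.

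- Default order, no stopping, no absence: 0.056. Order alone does no harm.
- Random order with stopping (mean 8 sessions): 0.015.
- All in default order with stopping: 1.00, 0.995, 0.91, 0.59 at a mean of 6, 8, 12, 20 sessions.
- Half in default order: 0.57, 0.41, 0.24, 0.12. A quarter: 0.16, 0.09, 0.06, 0.03.
- Absence alone at 10, 20, 30, 40%: 0.13, 0.41, 0.72, 0.91.
- Half in default order with stopping and 20% absence: 0.05 to 0.09.

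Both models agree: the false-signal rate runs from nominal or below to near certainty, depending on rates the protocol does not give.

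**The case against.** A reader might infer that this ANOVA will report preferences that do not exist, with modules 4 and 5 appearing least favoured because they come last. The documents do not support that, for these reasons:

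- The highest rates need every case in default order at one module per session. The protocol repeatedly allows any order and lets several modules share a session. With half the cases in default order and 10% stopping, rejection is only about 0.16.
- Modules 1 and 2 are both the first in order and the family-dependent ones. Early stopping favours them and family absence penalises them, so rates for each mechanism alone overstate the joint effect.
- Family absence is limited by the caregiver criterion. That modules 1 and 2 are lost without family is inferred from the text naming only 3, 4 and 5. Module 5 is adjusted, not dropped.
- The article does not state the score, checklist version or case set for the ANOVA. Those details may be left to a fuller plan.
- Module preference is not listed under Specific Aims, no decision rule depends on it, and therapists are asked for their impressions directly in focus groups.

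All of this stands, and it limits the size and the stakes. It does not rescue the stated reading. Partial cancellation leaves a pattern still produced by opportunity (0.80, 0.72, 0.85, 0.76, 0.69 above), and a non-significant result would be no better evidence about preference than a significant one.

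**Conclusion.** The point holds as a fault of interpretation. The Plan of Analyses fixes a reading, therapist preference, that the protocol's own delivery rules do not allow the comparison to bear. Differences can arise, or be hidden, through default order combined with early stopping, through lack of family engagement, and through case need.

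The size cannot be fixed from the documents. With no preference, 30 cases and binary coverage, rejection ranges from about 5% or below (half the cases in default order with 5% stopping; or all in default order with 5% stopping and 10% absence) to over 90% (all in default order, one module per session, 10% or more stopping). Stopping, session-count, ordering and absence rates are all assumptions. The consequence is moderate: a secondary analysis in a pilot, but one whose stated conclusion would not follow from its result.

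**What to change.** 1. In the Plan of Analyses, describe the module comparison, and the descriptive ranking of modules that precedes it, as module delivery or reach rather than therapist preference.
2. Add a supporting model of module delivery with client and therapist effects that adjusts for sessions attended and family attendance. The post-session fidelity forms and clinic attendance records already collected supply the data.
3. State that this model still does not isolate preference. Client need remains mixed in, and family attendance is partly a result of module 1, which exists to bring families into sessions. For the same reason, do not simply restrict modules 1 and 2 to cases with a family-attended session, since that selects on module 1's own result.

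The cost is a change of wording, a little more analysis and a more modest conclusion. No new data are needed.
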